##### Contextual barriers and facilitators for implementation of GBG

2.4.1.5.

To assess possible contextual barriers and facilitators for implementation, along with their perceived strength as factors, teachers in the experimental group will rate the pragmatic context assessment tool (pCAT) (42). The instrument consists of 14 items regarding implementation barriers and facilitators drawn from the Consolidated Framework for Implementation Research (CFIR). Each item has two separate ratings. The first rating is used to determine if the statement is a barrier, neutral or facilitating factor. The second rating determines the strength of the factor, i.e., if the factor is considered to have a weak/no effect or strong effect. pCAT was translated and adapted to the study by the research group. It will be assessed at all three time points, although T3 will be the focal point for analysis as teachers will be more experienced with GBG and likely have a more accurate estimate of what factors are perceived to influence implementation.

#### Observer-rated measures

2.4.2.

To complement teacher-rated measures, blinded and independent observers will visit a subset of included classrooms. To reduce costs, only one classroom per grade will be observed at each time point. The observed classrooms will then be chosen at random from each grade level. If a school only has one class per grade, all classes will be observed in that school. Each of these classrooms will be observed once during the same 3-week measurement periods the teachers fill in questionnaires from T1–T3. Each observation takes approximately 30 min to conduct. Observers will be trained by attending a workshop where they practice using the measurements on video sequences of an elementary school classroom. The observers will also be given a manual with behavioral targets and definitions, along with a detailed description of all procedures.

Observers will be hired independently by the research group to not be affiliated with the municipality. To blind the observers, they will only be given general information about the study (e.g., a study about classroom climate), i.e., no information about the study’s design or there being an intervention will be provided. The schools will be given instructions to not conduct GBG-sessions during observations and to not reveal any elements of the study to the observers. While some artifacts of GBG may be visible (e.g., team posters), they should blend with other visual objects that are common in classrooms. No circumstance or procedure for unblinding has been deemed applicable, and no other blinding (e.g., for intervention providers) has been deemed possible at this point.

The observational procedure starts with observers rating on-task behavior using Planned Activity Check (PLACHECK) (43); counting the number of task-oriented students each 3-min interval. The observers simultaneously count the frequency of three different types of teacher response to student behavior: General praise (e.g., “Good job!”), behavior-specific praise (e.g., “Well done sharing those pencils!”), and behavioral corrections or reprimands (e.g., “Stop that!”). These measures are performed continuously for 20 min.

After at least 30 min in the classroom, the observer rates 10 items on a Swedish translation of the Classroom Atmosphere Measure. Using behavioral indicators, items are rated on a scale of 1–4, with the option of scoring 0 if the item is not possible to rate or not applicable. A previous study measured internal consistency at α = 0.92 and kappa coefficients ranging from 0.62 to 0.81 (44).

#### Fidelity

2.4.3.

Certified trainers in GBG observe teachers in the experimental group on nine occasions, three for every phase in GBG, during the school year. The trainers rate procedural fidelity at each observation, before, during, and after the GBG-session using a standardized form. Scores will be averaged for the observation sessions to create a score for procedural fidelity.

Due to previous difficulties, collecting data on dosage (e.g., frequency and duration of GBG-sessions) is no longer a part of the trainer’s usual practice. To ensure that there is some proxy for dosage, trainers are asked to collect data on dosage through a weekly chart that tracks whether the teacher has played GBG 3 times during the week or not. Further measures regarding dosage have not been judged as feasible.

Trainers may certify teachers at the end of the school year. The requirements for certification in GBG are participation in all three training sessions, conducting at least 60 GBG-sessions during the school year, being observed by a certified trainer at least nine times and judged to conduct sessions with enough fidelity. This will constitute a binary variable, serving as a general measure for what the trainers assess as being passable implementation quality, to complement procedural fidelity.

### Data analysis

2.5.

As this study aims to investigate the effects of introducing GBG under real-world circumstances, whether the sample is compliant to the intervention or not, data analysis of the primary and secondary outcomes will follow intention-to-treat (ITT) procedures. The primary objective can be described as the difference in change over time in conduct problems between the group receiving GBG and the group receiving BAU. This can be expressed as a general linear model where conduct problems would signify the primary outcome of interest (denoted as 
Y
), with intervention group, time, and stratification variable (sociodemographic index score) being converted to dummy-scores and denoted as 
$\beta_{1}$
, 
$\beta_{2}$
, and 
$\beta_{3}$
 respectively, using an interaction term (
$\beta_{1}\times \beta_{2}$
) for intervention group and time. This approach entails some statistical considerations. One consideration is adjusting for the standard errors being affected by clustering (45). Since the municipality only has capacity to implement GBG in a low number of schools, considerations have to be made regarding the degree of precision in statistical models with few clusters. One option is to use a Bayesian ITT-model, which could render more precise estimates compared to corresponding frequentist models as long as default naïve priors aren’t used (46). Data for priors may be limited, particularly for some of the secondary outcomes, in which case weakly informed priors will be used. The estimates can also be compared with the corresponding frequentist ITT-analysis. As priors can have notable effect on estimates (47), sensitivity analyses will be conducted.

Analyses for secondary outcomes, including observational measures, will in large follow similar procedures, i.e., as outcomes in linear univariate models. Statistical analyses related to implementation will be treated differently. To assess implementation as a moderator, a parameter for procedural fidelity will be added to the statistical model for the primary analysis. Note that this is contingent on the chosen proxy for implementation to have some degree of variation. An earlier study reported high procedural fidelity across the board, with only dosage being suboptimal (21). This indicates that dosage may be a more potent moderator to investigate compared to procedural fidelity. Due to the previously mentioned difficulties in collecting data on dosage, the teacher-rated variable for number of GBG-sessions last week may be used as a proxy for dosage instead of the trainer-collected data on number of GBG-sessions for the school year.

While all data collection is handled by employees who have the same or similar formal requirements, the theoretical requirements of data “missing completely at random” are high. It is also possible that data could be “missing at random”, but in this case there are many unobserved variables that could potentially explain systematic differences between missing and observed data. Should missing data occur, it will primarily be assumed as “missing not at random”. Consequently, listwise deletion will be the default option to handle missing data. Multiple imputation will also be considered in cases where arguments can be made for data being missing at random, or where inclusion of auxiliary variables is deemed suitable. However, no measured variables in this study are currently expected to predict or correlate with potential missing data.

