### Design

2.1.

The study is a parallel group, cluster-randomized controlled superiority trial. Schools will be chosen as the unit of randomization to minimize contamination effects and to follow the municipality’s chosen strategy for implementation. This chosen strategy implements GBG in all K–3 (typically corresponding to children aged 6–9) classrooms simultaneously in every included school, rather than allowing for implementation in single classrooms in different schools. The group ratio will be 1:1 and randomization will be stratified using an aggregated sociodemographic index score used by the municipality to allocate school funding.

As the study and intervention lasts for a Swedish school year (August to June the following year) randomization will be conducted in May, before the end of the preceding school year. This is to ensure that schools have a similar amount of time to prepare for GBG as corresponding to their usual practice, as well as allowing the research group time to prepare all schools for data collection procedures. Randomization will be conducted and implemented by the research team. After recruitment all schools will be stratified as higher or lower than the city average on the stratification variable, i.e., the municipality’s sociodemographic index score, which has a centered mean at 100. Following this procedure, schools will be assigned a computer-generated number between 0 and 1 using the statistical software SPSS (RRID:SCR_002865), where schools with the highest numbers in each stratum will be placed in the intervention group. The research group will then notify schools of their study allocation, which will either be the intervention group who will receive training in GBG, or the control group, who will be conducting BAU. Schools in the control arm will be offered GBG-training in the following school year as an incentive to participate. GBG will be conducted by teachers who receive training during the study from certified GBG-trainers provided by the municipality.

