Measurements will primarily be concentrated along three timepoints, with each data collection period being limited to three weeks: Baseline (T1), 3-month follow-up (T2), and 9-month follow-up (T3 – primary endpoint). This corresponds to training in GBG which is spaced within the duration of a Swedish school year. Baseline measurements will be conducted post-allocation, just before start of training and intervention, to ensure the inclusion of all newly enrolled students. Data is primarily collected through teacher-rated, observer-rated, and trainer-rated measurements, though trainer-rated measures are collected continuously and not constricted to the 3-week measurement periods. A list of measures and their sequence are summarized in the SPIRIT-figure (Figure 1). All measures are collected on a classroom level. The study will be set at Sweden’s third largest municipality (Malmö), who is currently piloting the preventive framework Communities That Care (CTC) (30). See the trial registration on ClinicalTrials.gov (NCT05794893) for more details on study sites.

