##### Conduct problems

2.4.1.1.

The primary outcome for this study is conduct problems in the classroom. This will be measured using the scale “Problem Behavior in the Classroom Last Week,” listing 20 items concerning conduct problems commonly found in school classrooms, e.g., verbal assault directed towards other students, disturbing or distracting other students, and physically assaulting other students. A secondary outcome is conduct problems in school environments, which will be measured using the scale “Problem Behavior in the School Environment Last Week.” The scale remains similar to its classroom counterpart and consists of 15 items concerning conduct problems experienced in school common areas. For both scales, the teacher bases their ratings on the week prior to assessment and rates all items on a scale from 0 (no times last week) to 4 (several times a day). Both scales were translated from Norwegian to Swedish and have shown sound psychometric properties in previous Norwegian studies, with internal consistency at α = 0.88 and α = 0.84 for the respective classroom and school environment scales (37–39). Conduct problems will be assessed at all three time points.

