An additional consideration is that the primary outcome is teacher-rated and not blinded. This is only partially addressed using blinded and independent observers as they only observe a subset of classrooms due to financial limitations, specifically one classroom for each grade in each school. The blinded measures will still serve an important role in corroborating teacher-rated outcomes, with discrepancies between observer-rated and teacher-rated measures potentially implying weaker effectiveness. For example, positive changes in teacher-rated measures, but not in observer-rated measures, could potentially imply rater bias or that changes in behavior have not generalized outside of game sessions. Another possible limitation is that the study assesses change in multiple outcomes, meaning multiple independent comparisons. This could potentially increase the risk of type I error but should be ameliorated by having pre-specified a primary outcome, primary endpoint, and methods for data analysis. The breadth of outcomes also allows for the evaluation of more positive goals. For example, conduct problems could in theory be suppressed by using highly aversive or restrictive methods, but such methods would likely have detrimental effects on other outcomes assessed in this study.

In conclusion, this trial should inform the literature on how an adapted version of GBG fares in a naturalistic scenario. This has implications for how preventive interventions with high reach can be disseminated and adopted in order to reduce the risk factor of early conduct problems.

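### The primary contrast is a difference in change from T1; adjusting for the class's own T1 score is more precise and far less dependent on chance T1 imbalance, though not uniformly less biased

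*Protocol article*

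**What the plan says.** Section 2.5 (Data analysis) sets the contrast: "The primary objective can be described as the difference in change over time in conduct problems between the group receiving GBG" and the group receiving usual practice. It gives a linear model "with intervention group, time, and stratification variable (sociodemographic index score) being converted to dummy-scores and denoted as" three coefficients, plus a group-by-time interaction. T1 enters as one of the outcome waves (section 2.4.1.1: "Conduct problems will be assessed at all three time points"). No baseline covariate is mentioned, and no constraint that the arms share a T1 mean.

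On timing, section 2.1 (Design) says that "randomization will be conducted in May, before the end of the preceding school year" and that "The research group will then notify schools of their study allocation". T1 comes later: "Baseline measurements will be conducted post-allocation, just before start of training and intervention, to ensure the inclusion of all newly enrolled students". Section 3 (Discussion) acknowledges that "the primary outcome is teacher-rated and not blinded", but does not consider what this means for the T1 rating that the primary contrast subtracts.

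On the unit and sample, section 2.1 states that "All measures are collected on a classroom level". Section 2.2 expects about 3-5 intervention schools, hence about 6-10 in total at 1:1. It adds that the power analysis was not updated for the classroom-level design.

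**The concern.** With a free group difference at T1, the T3 interaction is a difference-in-differences. It subtracts the full T1 difference between arms, although a T1 difference predicts only a fraction r of itself at T3. The excess subtraction is noise. In a trial that concedes limited power and has few schools, that noise costs precision. A chance T1 imbalance also moves the estimate in a predictable direction.

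A second question is whether T1 is a clean baseline. Schools know their arm before teachers complete it, so the rating could be shifted by that knowledge. How such a shift reaches the estimated effect depends on the estimator and on whether the shift lasts until T3.

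**Working it through.** The article states no power, SD, ICC, T1-T3 correlation or number of classes per school, so there is no figure of its own to reproduce. Taken from the article are the contrast, the model terms, the timing of T1, the classroom unit, and 3-5 schools per arm. Everything else below is an assumption shown over a range.

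**1. Precision.** Let s be the common SD at T1 and T3, and r their correlation.
- Change analysis: variance proportional to 2(1-r)s².
- T1-adjusted analysis: proportional to (1-r²)s².
- Ratio: (1-r²)/[2(1-r)] = (1+r)/2.

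| r | variance ratio | SE reduction | ratio in simulation |
|---|---|---|---|
| 0.3 | 0.65 | 19% | 0.66-0.68 |
| 0.5 | 0.75 | 13% | 0.74-0.77 |
| 0.7 | 0.85 | 8% | 0.86-0.88 |
| 0.9 | 0.95 | 2.5% | 0.96-0.995 |

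The simulation used 4000 runs per setting, 3 or 5 schools per arm, 6 classes per school, ICC 0.05 or 0.15, stratum in both models, and the same r at school and class level.

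**2. Chance imbalance.** Per unit of T1 imbalance, the change estimate moves by -(1-r). In the simulation this was about -0.7, -0.5, -0.3 and -0.1 at r = 0.3, 0.5, 0.7 and 0.9. The adjusted estimate moved by no more than 0.03 in either direction.

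As an indication of size, assume ICC 0.10 and 7 classes per school. The SD of the T1 imbalance with K schools per arm is sqrt(2 × (0.10 + 0.90/7)/K) = 0.30 SD for K=5 and 0.39 SD for K=3. At r=0.6 a one-SD imbalance then moves the change estimate by 0.4 × 0.30 = 0.12 SD to 0.4 × 0.39 = 0.16 SD. These values ignore stratification, so they are upper values if the sociodemographic index predicts conduct problems.

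This is not a further loss on top of step 1. Since 2(1-r) - (1-r²) = (1-r)², the extra variance of the change analysis is exactly the variance due to imbalance.

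**3. Reporting shift from knowledge of allocation.** Suppose the GBG arm's ratings are shifted by b at T1 and by kb at T3.
- Change analysis: bias (k-1)b.
- Adjusted analysis: bias (k-r)b.
- Unadjusted T3 contrast: bias kb.

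With b = 0.3 SD and r = 0.6 (simulation with 4 schools per arm, 6 classes per school, ICC 0.10):
- Shift at T1 only (k=0): change -0.295 SD and adjusted -0.177 SD, both a false benefit. Theory gives -0.30 and -0.18.
- Same shift at T3 (k=1): change 0.00, adjusted +0.12 SD against GBG.

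Setting |k-r| equal to |k-1| puts the crossover at k = (1+r)/2, which is 0.8 at r=0.6. Adjustment has the smaller bias below that value and the larger bias above it.

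**4. Limits on the precision gain.**
- *School-level r above class-level r.* With 0.9 and 0.6, one pooled slope, 4 schools per arm and ICC 0.15, the SDs were 0.266 (change) and 0.258 (adjusted), a variance ratio of (0.258/0.266)² = 0.94. The estimates moved by -0.24 and +0.13 per unit of imbalance. This is one setting only; the gain is not guaranteed for wider gaps.
- *T1 entered as a school mean.* A school-level degree of freedom is lost. The approximate ratio of confidence-interval widths (adjusted to change) is 1.5-1.9 with 3 schools per arm, 1.0-1.2 with 4 and 0.91-1.10 with 5. The covariate must therefore be the class's own score.

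**The case against.** The strongest reply is that nothing in section 2.5 is wrong. Under randomization, a difference in change is an unbiased analysis of the same treatment effect, so this is a choice of estimator rather than a mis-stated estimand. The section's wording is also loose, and a fuller analysis plan may exist. This stands as a limit on severity. The article nevertheless names the contrast and the model terms, and the Discussion relies on pre-specified analysis methods to limit type I error, so the choice is fairly open to comment.

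A reader might infer that baseline adjustment is simply the less biased analysis because T1 was unblinded and post-allocation. The article does not support that. Nothing in it shows that teachers rated differently at T1 in anticipation of training. Teachers rate T3 unblinded as well, so a persistent shift is as plausible as a transient one, and for a persistent shift the change contrast does better. Nor is an unadjusted T3 contrast free of bias, since it carries any T3 shift in full.

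The article also has a partial safeguard: blinded observers visit a random subset of classrooms at T1, T2 and T3 (section 2.4.2), and the Discussion treats teacher-observer discrepancies as possible rater bias. The check is incomplete, because it covers one class per grade and uses different instruments, but it does reach T1.

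Finally, data collection is complete, so changing the primary analysis now is more than a matter of wording. That affects how the change is made. It does not touch the precision argument.

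**Conclusion.** The point holds on precision and on dependence on chance imbalance, which are one loss seen from two sides. Over r from 0.3 to 0.9, adjusting for T1 removes about 35% down to 5% of the variance of the change analysis. This assumes equal SDs at T1 and T3 and similar correlations at school and class level. The gain is smaller if school-level correlation is the higher, and can turn into a loss if T1 enters only as a school mean. The size cannot be fixed from the article, because r, the ICC and the number of classes per school are not given.

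On reporting bias there is no general winner: adjustment passes on r of a shift confined to T1 instead of all of it, but leaves (1-r) of a shift that persists, where the change contrast leaves none. The planned analysis is not invalid. It is a weaker choice than one available from data already collected, in a trial with few schools and admittedly low power, and it should be changed.

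**What to change.** Make the primary effect the group difference in T3 conduct problems adjusted for the class's own T1 score, entered at classroom level and not as a school mean, and for stratum, with clustering by school handled as planned. A repeated-measures model with the T1 means constrained equal across arms serves the same purpose.

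Keep the difference in change and an unadjusted T3 contrast as planned sensitivity analyses. The three respond differently to a transient and to a persistent reporting shift, so divergence among them is informative. Read them alongside the blinded observer data at T1-T3.

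No new data are needed: T1 is already collected in both arms. The statistical cost is one class-level degree of freedom. The procedural cost is a dated amendment, justified and disclosed through the route in section 5 (Trial status) and made before arm-level results are seen. If such results have already been seen, report the adjusted analysis as post hoc.

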### Selection of subjects

2.2.

To follow usual practice for the intervention, eligible schools are those with students in grades K–3. Exclusion criteria consist of schools where classrooms are already implementing GBG or schools who primarily have special education classrooms. However, inclusive classrooms using the standard Swedish curriculum with a few students receiving special education may still be included.

Recruitment will also follow usual conditions for the municipality, which in this case means that recruitment will be headed by trainers and facilitators working with CTC. The intervention and consequent participation in the study will first be offered to eligible schools in pilot areas for CTC. Schools with matching risk and protective factors according to CTC will be prioritized. Due to GBG already being implemented in several pilot areas, only a few schools are expected to sign up at this phase. As such, recruitment will be broadened in a second stage where GBG and participation in the study is offered to all remaining eligible schools in the municipality. Interested schools will then be jointly assessed for eligibility by the municipality and the research group. In the case of unsuccessful recruitment, other geographically close municipalities could be included in the recruitment phase.

In order to maximize statistical power for this sample, the number of recruited schools need to remain at the municipality’s maximum capacity for simultaneously implementing GBG, which is roughly 3–5 new schools at the time of the study for the intervention group. This corresponds to approximately 450–750 students based on typical school and class sizes in the area. It is important to note that this sample size was judged as acceptable with an earlier design and power analysis for this study that included individual level variation. However, this power analysis has not been updated for the current design that measures primarily on a classroom level, which is likely to yield lower statistical power, even with the intervention group at full capacity.

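### With about 6–10 randomised schools, the frequentist intention-to-treat test is not protected: few clusters is treated as a precision question and no small-sample inference is fixed

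*Protocol article*

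**What the plan says.** Section 2.1 (Design) makes the school the randomised unit: "Schools will be chosen as the unit of randomization to minimize contamination effects". It also fixes the ratio and strata: "The group ratio will be 1:1 and randomization will be stratified using an aggregated sociodemographic index score". Section 2.2 (Selection of subjects) gives the municipality's capacity as "roughly 3–5 new schools at the time of the study for the intervention group". Outcomes are classroom-level and collected at T1, T2 and T3 (9 months), with T3 the primary endpoint.

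Section 2.5 (Data analysis) defines the target as the group difference in change over time and continues: "This can be expressed as a general linear model where conduct problems would signify the primary outcome of interest". The displayed terms are dummy-coded group, time and stratum, plus group by time. Two caveats follow. The first is "One consideration is adjusting for the standard errors being affected by clustering". The second is that, because capacity limits the number of schools, "considerations have to be made regarding the degree of precision in statistical models with few clusters". The response to the second is a Bayesian intention-to-treat model, described as one option and justified by more precise estimates. Weakly informed priors are for outcomes where prior data are limited. The frequentist analysis is something the estimates can also be compared with.

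The Abstract puts it the other way round: a frequentist intention-to-treat analysis, with estimates compared against a Bayesian model using weakly informative priors. The Discussion counts pre-specified analysis methods among its safeguards against type I error.

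**The concern.** With 3–5 schools per arm, the frequentist danger is standard errors that are too small and a reference distribution with too many degrees of freedom. Section 2.5 presents the matter as one of precision, which points towards narrower intervals. A valid analysis with this few clusters will generally give wider ones.

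The sentence about adjusting standard errors does not settle this, because common ways of carrying it out fail here. The group-by-time contrast is a comparison of change between schools, so its error depends on how much schools differ in their change over time. Random intercepts for school and classroom remove stable differences only. Uncorrected sandwich errors are unreliable with 6–10 clusters. School-wide implementation makes school-level differences in change plausible.

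At stake is the error rate of the primary p-value and the coverage of its interval. The article also does not settle which analysis leads. Section 5 (Trial status) says data collection is complete, and the Discussion says pre-registration before recruitment was not possible, so the choice should not stay open.

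**Working it through.** The article gives no alpha, intraclass correlation, SD, effect size or power figure for the current design, so there is no stated figure to reproduce.

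**Inputs from the article**
- Schools: 3–5 in the intervention arm; at 1:1 the total is 2 × 3 = 6 to 2 × 5 = 10 (derived).
- Students: 450/3 = 750/5 = 150 per school.
- Three time points, with T3 primary.

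**Assumptions not in the article**
- Two-sided alpha of 5%.
- 7 classrooms per school: 150 students over four grades, about 21 per class.
- Base variance shares: school 0.10, school by time 0.05, classroom 0.40, residual 0.45 (total 1.00). The school-by-time share was varied from 0 to 0.10.

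**Hand check of random intercepts only (4 schools per arm, 28 classrooms per arm)**

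Stable school and classroom effects cancel in T3 − T1. With school-by-time share v and residual share e, the true SD of the contrast is √[2 × (2v/4 + 2e/28)]. A model without a school-by-time term puts v into the residual, so its standard error is about √[4 × (v + e)/28]. With v + e = 0.50 this is √0.0714 = 0.267 throughout.

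| v | e | True SD | SE ÷ true SD | Rejection under the null |
|---|---|---|---|---|
| 0 | 0.50 | √[2 × (0 + 0.0357)] = 0.267 | 1.00 | 5% |
| 0.05 | 0.45 | √[2 × (0.025 + 0.0321)] = 0.338 | 0.79 | 2 × [1 − Φ(1.96 × 0.79)] ≈ 12% |
| 0.10 | 0.40 | √[2 × (0.05 + 0.0286)] = 0.396 | 0.67 | 2 × [1 − Φ(1.96 × 0.67)] ≈ 19% |

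The number of schools cancels from the ratio, so moving from 3 to 5 schools per arm does not help.

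**Simulated type I error at nominal 5% (base shares, 2,000 null runs per setting)**

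| Analysis | 3 per arm | 4 per arm | 5 per arm |
|---|---|---|---|
| Cluster-robust SE, normal reference | 14.6% | 11.1% | 9.4% |
| School + classroom random intercepts | 12.8% | 12.6% | 12.4% |
| Displayed model, no adjustment | 3.8% | 4.0% | 3.4% |
| t-test on school-level T3 − T1 change | 4.4% | 5.0% | 4.9% |

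- At 4 per arm, random intercepts give 5.1% with a school-by-time share of 0 and 19.8% with 0.10. At the base shares the simulated SD is 0.342 against a mean model SE of 0.263, in line with the hand check.
- In a further simulation, cluster-robust errors with a normal reference rejected 9–16% at every variance split tried. A t reference on schools minus 1 brought this to 6–9%.
- In a separate simulation (4,000 runs per setting, 6 or 10 schools), the school-level t-test stayed at 4.5–5.6%. The unadjusted fit ranged from 0.2% (stable school and classroom variance, no school-by-time variance) to 14% (school-by-time 0.10, no classroom variance).

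**Cost in degrees of freedom**

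For 6 to 10 schools the school-level test has 4 to 8 df, with critical values 2.78 to 2.31. With a stratum term it has 3 to 7 df, with critical values 3.18 to 2.36. Against 1.96 the interval multiplier rises by 2.78/1.96 = 1.42 to 2.31/1.96 = 1.18, or 1.62 to 1.21 with the stratum term.

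**The case against.** A reader might infer that the primary standard errors are simply wrong because the displayed model has no school or classroom term. The article does not support that. It says only that the objective can be expressed in this form, and it goes straight on to adjusting standard errors for clustering. It nowhere says that an unadjusted fit will be run, and it does not call the model fixed-effects. Under the base assumptions an unadjusted fit would in any case be slightly conservative.

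A reader might also infer that one time parameter blurs the T3 effect. A single post-baseline dummy would indeed turn effects of 0 at T2 and −0.5 SD at T3 into −0.25 SD. But dummy-coding three time points normally gives two dummies, the hypotheses separate 3 from 9 months, and T3 is named primary. This is an ambiguity of notation, not an error.

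Two further objections have weight. Every variance share is assumed, and the random-intercept inflation disappears if schools do not differ in their change. Also, random-effects structure and degrees of freedom are commonly left to an analysis plan, and one may exist. The Bayesian route, with non-default priors and sensitivity analyses, is moreover a deliberate response to few clusters.

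What survives is in the text itself. Section 2.5 frames the problem as precision, it and the Abstract do not agree on which analysis leads, and the Discussion relies on pre-specified methods that section 2.5 leaves as options. The cluster-robust result does not depend on the school-by-time share.

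**Conclusion.** The point holds in a limited form and is a cheap improvement. With about 6–10 randomised schools, the frequentist test named in the Abstract is not protected by what section 2.5 commits to. Under 7 classrooms per school and the assumed shares, uncorrected cluster-robust inference would run at about 9–16% instead of 5% whatever the school-by-time share. Random intercepts alone would run at about 12–20% if that share is 0.05–0.10 and about 5% if it is zero. Inference from school-level change holds about 5% throughout. The size of the inflation rests on these assumptions. That the article fixes no small-sample method and no lead analysis does not.

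**What to change.** In section 2.5, and in any analysis plan:

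- State that the primary frequentist test is the single group contrast in T3-versus-T1 change, with time as a three-level factor.
- Base its inference on between-school variation in change with small-sample degrees of freedom. Use either a school-level analysis of T3 − T1 change with a t reference, or a mixed model with school, school-by-time and classroom effects and Kenward-Roger degrees of freedom. The simulations reported here cover the first. If the mixed model leads, report the school-level analysis as a check.
- State that uncorrected sandwich errors and random-intercept-only models will not be the primary inference.
- Give the Bayesian model the same random-effects structure.
- Say which analysis leads, so that the Abstract, section 2.5 and the Discussion agree.

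The change is to wording and needs no new data. The price is wider intervals, by roughly the multipliers shown above for the reference distribution alone, and correspondingly lower power in a trial that already acknowledges limited power.
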